### Exclusion criteria

Patients aged<18 years old.Patients whose synovial fluid is not available through preoperative aspiration or intraoperatively.Patients undergoing a failed one-stage revision surgery caused by subsequent PJI.Patients who have a follow-up period of less than 1 year.Patients visiting the hospital with an antibiotic-loaded cement spacer in their joints.Patients with a long preoperative history of antibiotic treatment.Patients who have undergone multiple surgeries on the same joint.Patients with a history of inflammatory joint diseases, such as rheumatoid arthritis and ankylosing spondylitis.Patients with active infection of other parts of the body or serious systemic infection.Patients with malignant tumour or severe disease of the cardiovascular system, pulmonary system or other system.Diabetic patients with poor glucose control.

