## Methods

### Study design and objectives

This single-centre trial is designed as a prospective diagnostic study. The objectives of this study are to supplement and improve the results of the preceding prospective study and to validate the feasibility of the 2018 new PJI definition for Chinese patients. The study is nonrandomized, and all patients serve as their own controls. From October 2019 to October 2020, we will recruit patients who agree to participate in the trial in the Department of Orthopaedics of the Chinese PLA General Hospital (301 hospital). Blood samples, synovial fluid samples and intraoperative findings will be collected for patients meeting the inclusion criteria. All of the samples and clinical data will be processed and analysed by a double-blind method. The major criteria of PJI (a sinus tract communicating with the joint or two positive cultures of the same organism) are identical among various diagnostic criteria [10–14, 16]. Therefore, we will use the major criteria as the gold standard to divide the enrolled patients into a PJI group and an Aseptic group. Then, we will compare the diagnostic efficiency of the respective minor criteria among the 2018 new definition (before revision and after revision), the MSIS criteria, the ICM criteria and the IDSA (Infectious Diseases Society) criteria (Tables 1, 2, 3, 4 and 5) [10–14, 16]. All patients included in our study will be followed for at least 1 year.

**Table 1 Tab1:** New scoring based definition for periprosthetic joint infection (PJI)

Major criteria (at least one of the following)				Decision
Two positive cultures of the same organism				Infected
Sinus tract with evidence of communication to the joint or visualization of the prosthesis				
Preoperative Diagnosis	Minor criteria		Score	Decision
	Serum	Elevated CRP or D-Dimer	2	≥6 Infected 2–5 Possibly Infected^a^ 0–1 Not Infected
		Elevated ESR	1	
	Synovial	Elevated Synovial WBC or LE	3	
		Positive Alpha-defensin	3	
		Elevated Synovial PMN (%)	2	
		Elevated Synovial CRP	1	
Intraoperative Diagnosis	^a^Inconclusive pre-op score or dry tap		Score	Decision
	Preoperative Score		–	≥6 Infected 4–5 Inconclusive^b^ ≤3 Not Infected
	Positive Histology		3	
	Positive Purulence		3	
	Single Positive Culture		2	

Proceed with caution in: Adverse local tissue reaction, crystal deposition disease, slow growing organisms

^a^For patients with inconclusive minor criteria, operative criteria can also be used to fulfill definition for PJI

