### Primary outcome

The diagnostic efficiency (sensitivity) of PJI with the minor criteria of the 2018 new definition (before and after revision).

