### Inclusion criteria

Patients who meet the major criteria of the new definition, that is, patients who have a sinus tract communicating with the joint or two positive cultures of the same organism in tissue or synovial fluid, will be included in the PJI group.Patients who undergo a one-stage revision surgery for aseptic reasons (with no evidence of sinus tracts or two identical positive cultures) will be included in the Aseptic group.

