**Fig. 1 Fig1:**
[figure not shown]
Study flow diagram. The process of recruitment, intervention, follow-ups, data collecting and statistical analysis in our study is presented. PJI = periprosthetic joint infection

A venous blood sample and synovial fluid sample will be obtained from the patients before surgery. After admission, a blood sample will be extracted by a nurse and immediately tested by the Clinical Laboratory of our hospital. The serum CRP, serum IL-6, serum D-Dimer levels and ESR will be determined. Generally, synovial fluid samples will be extracted from PJI patients by an experienced resident physician before admission. Portions of the extracted synovial fluid will be sent to the Division of Microbiology for the culture of microorganisms and to the Clinical Laboratory for routine synovial tests. Therefore, we will acquire the culture results, drug sensitivity results, synovial WBC counts and synovial PMN% when patients visit the hospital. The remaining synovial fluid will be centrifuged and stored in a − 80 C freezer for further study [17]. A drop of centrifuged synovial fluid will be obtained to examine LE [18] (Fig. 2). Importantly, we will not preoperatively extract synovial fluid from patients in the Aseptic group to prevent iatrogenic infection. Therefore, we will not take the culture results before surgery into account when patients are included in the Aseptic group. If two positive cultures of an identical organism are found intraoperatively for a patient in the Aseptic group, the patient will be excluded from the Aseptic group and included in the PJI group instead.

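### The primary outcome is the sensitivity of the minor criteria only in PJI that meets a major criterion, which is narrower than the stated conclusions, and the follow-up exclusions discard usable data

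*Protocol article*

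**What the plan says.** **Reference standard and groups.** Under Study design and objectives: "we will use the major criteria as the gold standard to divide the enrolled patients into a PJI group and an Aseptic group". Under Inclusion criteria, the PJI group is "patients who have a sinus tract communicating with the joint or two positive cultures of the same organism in tissue or synovial fluid", and the Aseptic group is "Patients who undergo a one-stage revision surgery for aseptic reasons (with no evidence of sinus tracts or two identical positive cultures").

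**Primary outcome.** "The diagnostic efficiency (sensitivity) of PJI with the minor criteria of the 2018 new definition (before and after revision").

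**Tables 1 and 2.** One major criterion is enough for the decision Infected. The minor score is used when no major criterion is met.

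**Follow-up.** Study design and objectives states: "All patients included in our study will be followed for at least 1 year". The Exclusion criteria list "Patients who have a follow-up period of less than 1 year", without limiting it to one group, and "Patients undergoing a failed one-stage revision surgery caused by subsequent PJI".

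**Reclassification.** Recruitment and intervention has one rule that moves a patient between groups. It begins "If two positive cultures of an identical organism are found intraoperatively for a patient in the Aseptic group" and sends that patient to the PJI group.

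**Conclusions claimed.** The abstract's Conclusion and the closing Conclusion both say that the study will validate the 2018 definition and its modified version for Chinese patients and identify the best way to diagnose PJI.

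**The concern.** Three points bear on who enters the sensitivity denominator.

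1. A patient revised for suspected infection, with no sinus tract and fewer than two matching cultures, fits neither group. In the final classification under Tables 1 and 2, these are the patients in whom the minor score decides. A sensitivity estimated without them says nothing direct about them, yet the conclusions are worded for PJI in general.

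2. The 1-year rule makes sense for Aseptic patients, in whom a year without infection supports the label. It has no such function in the PJI group, where a PJI patient with eight months of follow-up has the same information for the primary outcome as one with twelve.

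3. If the failed-revision exclusion operates after enrolment, two kinds of later evidence are handled differently: matching intraoperative cultures lead to reclassification, a later infection leads to deletion. A deleted patient who scored below the infected threshold may have been a false negative.

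At stake are the breadth of the claim, some primary-outcome data, and the visibility of possible missed infections.

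**Working it through.** **Step 1. The plan's own sample size.** Sample size gives a planning sensitivity of 94.9%, a planning specificity of 95.2%, 60 and 58 patients to analyse, and 63 and 61 after a 5% allowance. The article names no method. An exact (Clopper-Pearson) two-sided 95% interval with total width at most 0.13 needs n = 60 at 0.949 and n = 58 at 0.952, which matches; the method and the width are inferred. The allowance follows as 60 × 1.05 = 63 and 58 × 1.05 = 60.9, rounded to 61. The arithmetic is not in dispute.

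**Step 2. Which infections are counted.**

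| Infected patient | Where the rules put the patient |
|---|---|
| Sinus tract or two matching cultures | PJI group |
| Entered as Aseptic, two matching intraoperative cultures | Moved to PJI group |
| No major criterion, revised as infected | Neither group |
| No major criterion, revised as aseptic, infection appears later | Excluded, if the failed-revision rule is post-enrolment |
| No major criterion, revised as aseptic, no failure within 1 year | Stays in Aseptic group |

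Only the first two rows enter the sensitivity denominator, and both require a major criterion.

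The documents do not give the share q of infections without a major criterion, or the sensitivity s₀ of the minor criteria among them. As an illustration only, take 0.949 as the sensitivity in major-criterion PJI:

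sensitivity over all infections = (1 − q) × 0.949 + q × s₀

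- q = 0.1: 0.904 (s₀ = 0.5) to 0.944 (s₀ = 0.9)
- q = 0.4: 0.769 (s₀ = 0.5) to 0.929 (s₀ = 0.9)

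If s₀ equals 0.949, nothing changes. The documents fix neither the size nor the direction.

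**Step 3. Cost of the 1-year rule in the PJI group.** Recruitment and intervention has all blood, synovial, tissue and purulence data obtained by the end of surgery. The laboratory results come from those specimens, and neither the PJI label nor any index item uses follow-up. Exact limits are the 0.025 quantile of Beta(x, n − x + 1) and the 0.975 quantile of Beta(x + 1, n − x), with x = 0.949n:

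| n | Exact 95% interval | Width |
|---|---|---|
| 60 | 0.859 to 0.989 | 0.130 |
| 63 | 0.862 to 0.989 | 0.126 |
| 70 | 0.868 to 0.987 | 0.119 |

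The loss of precision is small. The 5% allowance covers withdrawal as well as loss to follow-up, so the difference between 63 and 60 is an upper figure for what this rule costs.

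**Step 4. Failed revisions, if excluded after enrolment.** Start from 57 of 60 detected (95.0%) and add k late infections. The documents give no value for k. A score below 6 is taken as not detected.

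| k | All scored below 6 | All scored 6 or more |
|---|---|---|
| 1 | 57/61 = 93.4% | 58/61 = 95.1% |
| 3 | 57/63 = 90.5% | 60/63 = 95.2% |
| 5 | 57/65 = 87.7% | 62/65 = 95.4% |

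For specificity, deletion and reclassification both take these patients out of the Aseptic denominator. With 55 of 58 remaining Aseptic patients negative, it is 55/58 = 94.8% either way. Leaving three patients who scored below 6 in the Aseptic group would give 58/61 = 95.1%, so in that case deletion does not flatter specificity.

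**The case against.** **The reference standard is a declared choice.** The article uses the major criteria because they are common to the criteria sets, and then compares the minor criteria against them. A label for infections without a major criterion would need another standard, and one built from minor criteria would reuse the index tests. This stands. It defends the design but not the wider conclusion.

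**The minor score is not redundant in the PJI group.** A reader might infer that sensitivity is measured only where the minor criteria are not needed, and that the infected patients who need them are exactly those removed. The documents do not support this. Table 1 has a separate preoperative score, which is informative when matching cultures appear only at surgery, and a missed infection that does not fail within a year stays in the Aseptic group.

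**The failed-revision exclusion is ambiguous.** It stands among baseline items such as age and cement spacers, and could describe patients who present after an earlier failed revision. The post-enrolment reading is more natural beside the 1-year rule and the one-stage definition of the Aseptic group, but it is not certain.

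**Late infection may be new infection.** The exclusion speaks of subsequent PJI, and nothing in the article separates an infection missed at surgery from one acquired later. Counting all of them as infected at surgery could wrongly lower sensitivity. This stands, and rules out making that the main analysis.

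**Deletion does not improve both measures.** A reader might infer that sensitivity and specificity are both flattered. Step 4 shows otherwise: specificity is the same under deletion and reclassification, and sensitivity is slightly higher with the late cases counted if they all scored 6 or more.

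**Conclusion.** The point holds in a limited form.

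- **Certain from the text:** the primary outcome is the sensitivity of the minor criteria in PJI that meets a major criterion. The two Conclusion sections claim more. How far sensitivity differs in other infections cannot be derived from the documents.
- **Certain from the text:** the 1-year exclusion reaches the PJI group, where follow-up serves neither classification nor scoring. It discards usable primary-outcome data. The cost is small: interval width of at most about 0.130 against 0.126. The article gives no evidence that short follow-up is related to outcome.
- **Conditional:** if the failed-revision exclusion is post-enrolment, possible missed infections disappear from the results. With three such patients (assumed), sensitivity would be 90.5% to 95.2%, against 95.0% without them. That range includes no bias.

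This should be corrected because the changes are nearly free, not because a large error has been shown.

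**What to change.** 1. Apply the 1-year follow-up requirement to the Aseptic group only. Keep PJI patients in the primary analysis whatever their length of follow-up. Cost: one line of eligibility wording.
2. State the primary result and both conclusions as the sensitivity of the minor criteria in PJI that meets a major criterion. Cost: a narrower claim.
3. State whether the failed-revision exclusion is a baseline criterion or is applied after enrolment. If after enrolment, keep these patients' data and prespecify a supplementary (sensitivity) analysis that counts them as infected, beside the main analysis without them. Report their number and scores, and note that some may be new infections. Cost: one extra analysis on specimens and follow-up already planned for enrolled patients.

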**Fig. 1 Fig1:**
[figure not shown]
Study flow diagram. The process of recruitment, intervention, follow-ups, data collecting and statistical analysis in our study is presented. PJI = periprosthetic joint infection

A venous blood sample and synovial fluid sample will be obtained from the patients before surgery. After admission, a blood sample will be extracted by a nurse and immediately tested by the Clinical Laboratory of our hospital. The serum CRP, serum IL-6, serum D-Dimer levels and ESR will be determined. Generally, synovial fluid samples will be extracted from PJI patients by an experienced resident physician before admission. Portions of the extracted synovial fluid will be sent to the Division of Microbiology for the culture of microorganisms and to the Clinical Laboratory for routine synovial tests. Therefore, we will acquire the culture results, drug sensitivity results, synovial WBC counts and synovial PMN% when patients visit the hospital. The remaining synovial fluid will be centrifuged and stored in a − 80 C freezer for further study [17]. A drop of centrifuged synovial fluid will be obtained to examine LE [18] (Fig. 2). Importantly, we will not preoperatively extract synovial fluid from patients in the Aseptic group to prevent iatrogenic infection. Therefore, we will not take the culture results before surgery into account when patients are included in the Aseptic group. If two positive cultures of an identical organism are found intraoperatively for a patient in the Aseptic group, the patient will be excluded from the Aseptic group and included in the PJI group instead.

**Fig. 2 Fig2:**
[figure not shown]
Management of synovial fluid and test results of leukocyte esterase (LE). The synovial fluid samples acquired preoperatively and intraoperatively are all centrifuged and divided into 3–4 samples. The centrifuged samples will be stored at − 80 C freezer for further study. Synovial fluid samples before centrifugation and after centrifugation are separately used for the test of LE. The results of LE test will be photographed and recorded

During the operation, we will collect three periprosthetic tissue samples from each patient for microorganism culture and three tissue samples for histological analysis. Meanwhile, synovial fluid will be intraoperatively collected and processed as described above. An experienced surgeon will record whether purulence is present in the articular cavity.

The stored synovial fluid of the patients will be numbered, and the details will be recorded by an investigator responsible for managing synovial fluid samples. The number of the synovial fluid sample should be identical to the number of the corresponding patient. Then, the synovial fluid will be delivered to an investigator blinded to the details of the sample who will measure the synovial alpha-defensin and synovial CRP levels by the ELISA (enzyme linked immunosorbent assay) method [19–21].

All of the above data will be delivered to an investigator for statistical analysis. The investigator will only receive the patient number and various indicator values and will determine whether the patient is suffering from PJI based on the test results using different diagnostic criteria. Five kinds of diagnostic criteria are shown in the Tables 1, 2, 3, 4 and 5. The patient meeting one of these criteria will be considered a PJI patient according to this criteria. Using the five diagnostic criteria, the investigator responsible for the statistical analysis will finally determine five diagnoses respectively corresponding to five diagnostic criteria for each patient. Statistical results will be sent to researchers for calculation of the primary and secondary outcomes.

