^b^Consider further molecular diagnostics such as next-generation sequencing

**Table 2 Tab2:** Proposed 2018 ICM criteria for PJI (modified version of the 2018 new definition)

Major criteria (at least one of the following)				Decision
Two positive growth of the same organism using standard culture methods				Infected
Sinus tract with evidence of communication to the joint or visualization of the prosthesis				
Minor Criteria	Threshold		Score	Decision
	Acute^b^	Chronic		Combined preoperative and postoperative score: ≥6 Infected 3–5 Inconclusive^a^ <3 Not Infected
Elevated CRP (mg/L)	100	10	2	
or				
D-Dimer (ug/L)	Unknown	860		
Elevated Serum ESR (mm/hr)	No role	30	1	
Elevated Synovial WBC (cells/μL)	10,000	3000	3	
or				
Leukocyte Esterase	++	++		
Or				
Positive Alpha-defensin (signal/cutoff)	1.0	1.0		
Elevated Synovial PMN (%)	90	70	2	
Single Positive Culture			2	
Positive Histology			3	
Positive Intraoperative Purulence^c^			3	

^a^Consider further molecular diagnostics such as Next-Generation Sequencing

^b^These criteria were never validated on acute infections

^c^No role in suspected adverse local issue reaction

**Table 3 Tab3:** Musculoskeletal Infection Society (MSIS) criteria proposed in 2011

Major criteria	
1. There is a sinus tract communicating with the prosthesis	
2. A pathogen is isolated by culture from at least two separate tissue or fluid samples obtained from the affected prosthetic joint	
Minor criteria	
1. Elevated serum erythrocyte sedimentation rate (ESR) and serum C-reactive protein (CRP) concentration	
2. Elevated synovial leukocyte count	
3. Elevated synovial neutrophil percentage (PMN%)	
4. Presence of purulence in the affected joint	
5. Isolation of a microorganism in one culture of periprosthetic tissue or fluid	
6. Greater than five neutrophils per high-power field in five high-power fields observed from histologic analysis of periprosthetic tissue at× 400 magnification.	

PJI exists when one of the major criteria occurs or four of the six minor criteria occur

**Table 4 Tab4:** International Consensus Meeting (ICM) criteria proposed in 2013

Major criteria	
1. Two positive periprosthetic cultures with phenotypically identical organisms	
2. A sinus tract communicating with the joint	
Minor Criteria	
1. Elevated serum C-reactive protein (CRP) and erythrocyte sedimentation rate (ESR)	
2. A single positive culture	
3. Elevated synovial fluid white blood cell (WBC) count or ++ change on leukocyte esterase test strip	

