4. Elevated synovial fluid polymorphonuclear neutrophil percentage (PMN%)	
5. Positive histological analysis of periprosthetic tissue	

PJI exists when one of the major criteria occurs or three of the five minor criteria occur

**Table 5 Tab5:** Infectious Diseases Society of America (IDSA) criteria

Definition of PJI	
1. The presence of a sinus tract that communicates with the prosthesis 2. The presence of acute inflammation based on histopathologic examination of periprosthetic tissue at the time of surgical debridement or prosthesis removal. 3. The presence of purulence surrounding the prosthesis. 4. Two or more intraoperative cultures or combination of preoperative aspiration and intraoperative cultures that yield the same organism. Growth of a virulent microorganism (eg, *S. aureus*) in a single specimen of a tissue biopsy or synovial fluid may also represent PJI. 5. The presence of PJI is possible even if the above criteria are not met; the clinician should use his/her clinical judgment to determine if this is the case after reviewing all the available preoperative and intraoperative information	

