### Secondary outcomes

The following will be assessed:

Specificity, true positive, true negative, false positive, false negative, positive predictive value and negative predictive value of the new definition (before and after revision).

Sensitivity, specificity, true positive, true negative, false positive, false negative, positive predictive value and negative predictive value of the MSIS criteria.

Sensitivity, specificity, true positive, true negative, false positive, false negative, positive predictive value and negative predictive value of the ICM criteria.

Sensitivity, specificity, true positive, true negative, false positive, false negative, positive predictive value and negative predictive value of the IDSA criteria.

The outcomes above are calculated from the data of patients’ medical record information and laboratory tests. We would like to summarize these outcome data as follows. Patients’ basic information such as demographics, comorbidities and surgery information will be collected first through reviewing patients’ medical records or asking patients themselves. Then we will collect data of serum indicators, synovial indicators and intraoperative indicators of each patient. Serum indicators consist of serum C-reactive protein (CRP), serum D-Dimer, serum interleukin-6 (IL-6) and erythrocyte sedimentation rate (ESR). Synovial indicators consist of synovial white blood cell (WBC), leukocyte esterase (LE), synovial alpha-defensin, synovial polymorphonuclear neutrophil percentage (PMN%) and synovial CRP. Intraoperative indicators consist of histology (pathological data from freezing tissue slices), existence of purulence and microorganism culture. These outcome data will be used to determine whether PJI occurs according to various criteria. Finally, we will acquire result of sensitivity, specificity, true positive, true negative, false positive, false negative, positive predictive value and negative predictive value of five diagnostic criteria of PJI. The concrete methods of data acquisition and processing are clearly introduced in the subsequent ‘Recruitment and intervention’ section.

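### The classification rule applies Tables 1–5 in full, against the minor-criteria index test set elsewhere, and the promised IDSA minor-criteria comparison is undefined

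*Protocol article*

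**What the plan says.** Study design and objectives fixes the reference standard: "we will use the major criteria as the gold standard to divide the enrolled patients into a PJI group and an Aseptic group". It then names the index test: "we will compare the diagnostic efficiency of the respective minor criteria among the 2018 new definition", and continues the list with MSIS, ICM and IDSA. It also states that the major criteria are the same in all of these definitions. The Primary outcome section agrees: "The diagnostic efficiency (sensitivity) of PJI with the minor criteria of the 2018 new definition (before and after revision".

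The Secondary outcomes section leaves the word minor out of every line, for example "negative predictive value of the MSIS criteria". It refers the reader to Recruitment and intervention for the methods of data acquisition and processing.

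That section contains the only operational rule. The analyst receives a patient number and indicator values and makes one diagnosis per criterion: "Five kinds of diagnostic criteria are shown in the Tables 1, 2, 3, 4 and 5", followed by "The patient meeting one of these criteria will be considered a PJI patient according to this criteria". These five diagnoses are then passed on to calculate the primary and secondary outcomes. Nothing tells the analyst to set the major criteria aside. The tables themselves include them; Table 3, for instance, ends "PJI exists when one of the major criteria occurs or four of the six minor criteria occur".

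Table 5 (IDSA) has no major and minor parts. Item 4 begins: "Two or more intraoperative cultures or combination of preoperative aspiration and intraoperative cultures that yield the same organism".

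**The concern.** The PJI group consists of patients who meet a major criterion. If the index test also counts a major criterion as positive, the reference standard sits inside the test being assessed. Sensitivity then reflects the enrolment rule and says little about the test.

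The primary outcome is a sensitivity, and the study is meant to find the best of five criteria. The text that states the aim and the text that produces the numbers give different index tests, and the one that produces the numbers leaves little or nothing to compare. For IDSA, even the intended reading cannot be carried out from the table as printed.

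**Working it through.** **Inputs.** Reference standard, index test and outcomes: Study design and objectives, Primary outcome, Secondary outcomes. Classification rule: Recruitment and intervention. Decision rules: Tables 1–5. Planning values: Sample size (sensitivity 94.9%, specificity 95.2%; 60 and 58 analysed; 63 and 61 after 5% loss; at least 70 per group).

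**Step 1. The plan's own figures.** An exact 95% interval of total width at most 0.13 needs n = 60 at 94.9% and n = 58 at 95.2%. The width is back-solved; the article does not state it, and other methods come close (a one-sided 5% test against 0.85 with 80% power gives 61 and 57). Then 60 × 1.05 = 63 and 58 × 1.05 = 60.9, rounded up to 61. The sample size does not decide this point. It does show that planning assumed a sensitivity below 100%.

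**Step 2. Full tables, all fields supplied.** Every PJI-group patient has a sinus tract or two matching cultures. Tables 1–4 call such a patient infected outright. Table 5 lists the same findings (item 1 and the first part of item 4); I read any one of its items as enough, since item 5 deals with the case where the others are absent. So FN = 0 and:

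- Sensitivity = TP/(TP + FN) = 60/60 or 70/70 = 100% for all five criteria.
- Exact 95% lower limit = 0.025^(1/n): 94.0% at n = 60, 94.9% at n = 70.
- Negative predictive value = TN/(TN + 0) = 100%.
- Difference in sensitivity between any two criteria = 0.
- Specificity does not change, because the Aseptic group excludes anyone who meets a major criterion.

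**Step 3. Full tables, sinus-tract status not passed on.** Sinus tract is not among the indicators in Secondary outcomes or Blind reading of outcomes; culture results are. Let c be the share of the PJI group with two matching cultures, and s the sensitivity of a given criterion in the rest. Then

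sensitivity = c + (1 − c)·s,

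and the difference between two criteria is (1 − c)·(s₁ − s₂). The documents do not give c. For any c above 0, sensitivity is raised towards 100% and differences shrink by the factor 1 − c, so the result depends on the enrolment mix.

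**Step 4. Minor criteria only.** Sensitivity is free to vary. If it were 94.9%, the exact 95% interval would be 85.9–98.9% at n = 60 and 86.8–98.7% at n = 70. The value is illustrative: the article does not say whether the retrospective 94.9% was scored on minor criteria alone.

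**Step 5. Table 5 item by item.**

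| IDSA item | Status |
|---|---|
| 1, sinus tract | Reference standard |
| 2, acute inflammation on histology | Usable |
| 3, purulence | Usable |
| 4, two or more cultures, same organism | Reference standard |
| 4, single specimen with a virulent organism | Not the reference standard; use not defined |
| 5, clinical judgement | Cannot be applied by an analyst who sees only numbers and indicator values |

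A subset can be built, but the article does not define one.

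**Step 6. Overlap that remains under minor criteria.** A patient enrolled on two matching cultures necessarily has a positive culture. If that scores the single-positive-culture item, the patient starts with:

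| Table | Credit from enrolment | Still needed |
|---|---|---|
| 1 (intraoperative step) | 2 of 6 points | 4 points |
| 2 | 2 of 6 points | 4 points |
| 3, MSIS | 1 of 4 items | 3 items |
| 4, ICM 2013 | 1 of 3 items | 2 items |

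If the item means exactly one positive culture, the patient scores nothing for it. The article does not say which applies.

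**The case against.** The strongest reply is that the design section already limits the comparison to minor criteria for all five definitions and the primary outcome repeats this, so the operational paragraph merely omits a word. Part of this stands: a reader might infer that the plan as a whole yields 100% sensitivity by construction, and the documents do not support that. The 100% is conditional on the operational rule prevailing and on sinus-tract status reaching the analyst. The reply does not remove the contradiction. Secondary outcomes names that paragraph's section as the place where the methods are set out, and its diagnoses feed the primary outcome. Nor is this detail that an article may leave to a fuller document, because the article gives the rule and gives it in a conflicting form.

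A reader might also infer that the new definition, scored on minor criteria at about 94.9%, would be set against MSIS, ICM and IDSA at 100%. That does not hold. The design section applies minor criteria to the comparators too, and Secondary outcomes drops the word for the new definition as well, which looks like shorthand. The 94.9% is also not known to be a minor-criteria figure.

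Finally, a reader might conclude that IDSA cannot be compared at all. That is too strong: items 2 and 3, and possibly the virulent-organism clause of item 4, could be scored. The accurate statement is that no form has been defined.

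**Conclusion.** The point holds as a contradiction on the index test that produces the primary outcome. If the operational rule is followed, every culture-defined PJI patient is positive on all five criteria, and sinus-tract patients too if that status is passed on. Sensitivity is then 100% (60/60 or 70/70) or is raised towards it by the culture-defined share, which the documents do not give. If the design section and primary outcome prevail, nothing is forced outright, but the single-culture overlap remains.

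The IDSA gap exists under the minor-criteria reading whichever way the contradiction is settled. The 100% result rests on reading the operational rule literally and, for IDSA, on one item being sufficient. Because the primary outcome is affected and the remedy is short, this should be settled before any patient is classified.

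**What to change.** 1. In Recruitment and intervention, state that for the accuracy analysis the analyst applies only the minor criteria, at each table's own threshold: a score of at least 6 for Tables 1 and 2, at least four of six for MSIS, at least three of five for ICM 2013. Add the words minor criteria to every line of Secondary outcomes.
2. For IDSA, either pre-define and label a modified IDSA built from items 2 and 3, saying whether the single virulent organism in item 4 counts, or drop IDSA from the sensitivity comparison. Limit the statement that the major criteria are identical to Tables 1–4.
3. State how a single positive culture is scored in patients enrolled on two cultures, for example by also reporting all results with that item left out.

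The cost is wording in three sections and some extra analysis. Sensitivities may be lower than under the full tables, but they would measure the minor criteria.
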